#### Intervention Format, Structure, and Content

Participants in both the UC and WL arms will continue to receive the standard of medical care from their PCPs and any specialists, per KPNC treatment protocols. In addition, they will receive an Omron HJ-7201ITC pedometer, which records steps taken, and an HBF-400 scale for home weight measurement. They will also receive KPNC standard asthma self-management and weight management educational handouts and a list of elective weight management services offered at the participating medical centers.

In addition to usual care, participants in the WL arm will progress through three successive intervention stages: Intensive, Transitional and Extended stages. Table 3 shows the design elements of the BE WELL intervention during the three stages.

**Table 3 T3:** Design elements of the BE WELL weight loss intervention

Stage	Intensive (Months 1-4)	Transitional (Months 5-6)	Extended (Months 7-12)
**Goal of contact**	Gradual weight loss associated with small, progressive changes in diet and physical activity		Weight maintenance or continued gradual weight loss
**Contact schedule**	Weekly (13 contacts)	Monthly (2 contacts)	Bi-monthly/monthly (typically 3-6 contacts)
**Contact mode**	Group, in person (Family member welcome)	Individual, in person (Family member welcome)	Individual, by phone (in person as needed)
**Contact duration**	90-120 minutes	30-60 minutes	Variable
**Contact structure**	* Private weigh-in * Review and sharing of progress, or lack thereof, in relation to action plan/goals from last session * Didactic presentation of a new topic * 30-minute supervised physical activity session * Development of individual action plan/goals for the next week	* Private weigh-in * Review of self-monitoring records * Identification of personal barriers to weight loss and activity * Problem solving and relapse prevention * Development/revision of a customized care plan	* Review of self-monitoring records * Detection of signs of non-adherence and relapse * Problem solving to encourage adherence and prevent relapse * Revision of the customized care plan * If indicated, re-initiation of intensive weight loss efforts through individual or small group visits

##### Intensive Stage

The Intensive stage of the BE WELL intervention is adapted from the Group Lifestyle Balance (GLB) program™ [66]. The GLB program is based on the highly successful Diabetes Prevention Program [57] and includes 12 weekly small group sessions. Each session follows a similar structure and includes five curriculum components: 1) measurement and recording of weight, 2) review of self-monitoring records and progress, 3) identification of personal barriers to weight loss and activity and potential solutions, 4) presentation of a new content area, and 5) goal setting and action plans for next week. In BE WELL, the GLB Manual of Operations will be closely followed, except for the addition of a food tasting activity as part of the check-in process and a 30-minute segment of physical activity demonstrations and practices at the end of each session. The food tasting activities are aimed at increasing participant experience with healthy food choices, encouraging them to try new foods that they might not normally try on their own, and stimulating a social, fun and engaging environment. The physical activity demonstrations and practices are aimed at increasing participant awareness of physical activity intensity, experiencing various moderate-intensity activities that are safe and that they can easily incorporate into their daily lives, and increasing participant confidence. As part of these supervised exercises, participants will learn how to recognize exercise-induced bronchospasm based on symptoms and peak flow meter readings and the appropriate prophylaxis and treatment. In BE WELL, participants will be given a pedometer and start using it to record their daily steps in week 1, as opposed to starting this in week 10 as in the original GLB program. Furthermore, BE WELL participants will attend an additional group session focusing on the latest evidence that came out after the GLB program on high-carbohydrate and high-fat/high-protein dietary approaches to weight loss to complement the program's emphasis on low-fat diets. The 13 group sessions of 90-120 minutes each will be delivered by a nutrition health educator and a fitness instructor over a 4-month period.

##### Transitional Stage

In the Transitional stage, participants will attend one individual counseling session in month 5 and another one in month 6. The goals of these visits are to 1) finalize a customized, comprehensive action plan for weight loss and maintenance viable in the participant's environment, and 2) facilitate participant independence in carrying out and maintaining that behavior change as the influence of the interventionists diminishes. During the sessions, interventionists will review and discuss the participant's self-monitoring records of weight, dietary intake and physical activity, provide feedback on progress (or lack thereof), discuss barriers to behavior change, and will advise on problem solving and relapse prevention strategies.

##### Extended Stage

The goal of the remaining 6 month will be to facilitate the continued evolution of behavior changes achieved to date and to promote long-term weight stability. Participants will continue to monitor their weight, dietary intake, and physical activity based on their care plan. Interventionists will monitor the progress of each individual and provide individualized feedback and structured guidance by phone at least bi-monthly. Participants may initiate contact with the interventionists at any point. At the discretion of the interventionists, participants may be seen in person to address outstanding issues related to poor understanding of and/or adherence to the intervention protocol. Participants with weight gains of 3 to 5 lbs (1.4 to 2.2 kg) will be telephoned on a biweekly basis until they return to a stable, lower weight. A weight gain of 5 lbs (2.3 kg) or more will automatically trigger a suggestion of an in-clinic visit at which the participant will be encouraged to restart or intensify active weight-loss efforts and a new action plan will be created to guide the efforts.

### Participant Safety

Participants will be carefully screened, and individuals for whom the intervention is deemed medically inappropriate or unsafe will be excluded. PCP approval will be required before potentially eligible patients are contacted by the study. During screening, women who are pregnant, lactating, or planning to become pregnant during the study period will be excluded. If a participant becomes pregnant during the study, she will be excluded from further participation in all study activities, and her PCP will be notified. Participants who are diagnosed with any other exclusionary condition (e.g., coronary heart disease, stroke, diabetes, cancer) following randomization may continue with the intervention (if applicable) and follow-up assessments only after explicit approval of a study physician.

Surveillance for adverse events and relevant clinical events will occur by questionnaire at regularly scheduled assessment points and by systematic query of all participants' electronic health records at three month intervals throughout the follow-up. Similar information reported by participants at other times (e.g., during intervention encounters) will be duly noted and followed up to assure participant safety. A study physician will review all adverse event reports to determine whether they are serious, study related, or expected, and the events will be reported to the IRB, DSMB, and the sponsor according to the reporting timelines appropriate to the type of the event.

Alert levels (e.g., for lung function and blood pressure) and alert conditions (e.g., asthma exacerbations, cardiovascular events, musculoskeletal injuries) and referral protocols have been established to ensure that participants are offered appropriate evaluation and therapy when clinically indicated. In all cases, participants may be immediately referred for medical evaluation as needed or recommended by the study clinician.

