### Retention

Adherence and retention in BE WELL is expected to be fostered by: 1) selection/retention of qualified staff, their training, and systematic quality control; 2) the relationship between staff and participants, 3) willingness to accommodate participant schedules and needs, and 4) resourcefulness and persistence of the staff. For purposes of follow-up assessment, a participant tracking database will be used to assure that participants are contacted on a timely basis. Subjects' contact information will be kept current and at least two alternative contacts will be collected. Subjects will be given a nominal payment for each data collection visit. Assessment staff, who will be blinded to treatment assignment, will contact subjects who miss a visit to reschedule the visit and to re-engage them in subsequent follow-ups. Subjects will be educated about the importance of follow-up assessment even if they are not adhering to the treatment. Priorities will be given to the primary and main secondary outcomes in cases where not all follow-up measurements may be obtained from a subject.

Ongoing monitoring of indices of participation in intervention activities helps interventionists identify participants who are having problems adhering to the intervention protocol and thus initiate recovery efforts. Such efforts can range from brief telephone discussion to an individual counseling session with the interventionist in which the participant who makes a decision to discontinue intervention can review concerns regarding BE WELL, reasons for staying in the study, and decisions about remaining a participant. Unless the participant declines, the interventionist will continue to contact the participant on a progressively less frequent schedule, starting monthly and decreasing to semi-annually to remind her/him of the opportunity to re-enter BE WELL.

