#### Statistical analysis

The primary hypothesis compares Juniper ACQ scores between the WL and UC arms at 12 months using an intent-to-treat analysis. Linear mixed modeling, using SAS PROC MIXED [67] will test time and group interactions to assess whether within-subject change in Juniper ACQ scores differs by condition (equation 3).(3)

Due to randomization, the distributions of baseline values on the dependent variable (Y_0_) and baseline covariates (X_i _where i = 1 to k) should be similar between treatment arms and thus not bias the analysis. Nonetheless, to the extent they are associated with the outcome, their inclusion in the model will account for otherwise unexplained variation and hence increase the efficiency of the analysis. In addition, their inclusion will guard against imbalance in the distributions of these covariates between treatment arms, which can still occur despite randomization. a, g, and δ represent the random effects caused by clustering of patients with physicians and, in turn, physicians within clinics, and by blocking of patients within medical centers. ε takes into account the correlation of repeated measures within subjects.

The same analysis strategy is appropriate for evaluating secondary aims where the hypotheses are identical but with different outcome measures (e.g., lung function, asthma-specific QoL, asthma-related HCU). The longitudinal effects of the intervention will be assessed using the same model, except that the focus is comparisons within the intervention arm at different time points. Analyses will also be conducted to examine whether there is a dose-response relationship between intervention adherence and outcome, where dose is defined in terms of number of group sessions attended, number of self-monitoring logs kept, average daily intakes of calories and fat, and average number of minutes of physical activity per week.

The primary analyses will be intention-to-treat. Secondary per-protocol or as-treated analyses will be performed to help elucidate the primary findings. For subjects with missing data at follow-up, we will conduct and report on sensitivity analyses in which several previously recommended approaches for handling missing data in longitudinal trials will be used, e.g., multiple imputation and the pattern-mixture model [68].

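### Pregnancy stops the 6- and 12-month ACQ outright, and a new exclusionary diagnosis makes it subject to approval, so the protocol creates avoidable gaps in an intention-to-treat primary outcome

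*Protocol article*

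**What the plan says.** All references are to the protocol article.

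- **Participant Safety, pregnancy.** For a woman who conceives after entry, the rule is that "she will be excluded from further participation in all study activities, and her PCP will be notified". The sentence does not carve out outcome assessments.
- **Participant Safety, other conditions.** Someone later found to have another exclusionary condition (heart disease, stroke, diabetes and cancer are the examples given) "may continue with the intervention (if applicable) and follow-up assessments only after explicit approval of a study physician". The parenthesis about the intervention shows that the rule also covers usual care, where there is no intervention to stop and the only thing restricted is assessment.
- **Statistical analysis.** The primary hypothesis "compares Juniper ACQ scores between the WL and UC arms at 12 months using an intent-to-treat analysis", and the section repeats: "The primary analyses will be intention-to-treat". On gaps it says: "For subjects with missing data at follow-up, we will conduct and report on sensitivity analyses", with multiple imputation and a pattern-mixture model as examples.
- **Retention.** "Subjects will be educated about the importance of follow-up assessment even if they are not adhering to the treatment". The same section gives the primary and main secondary outcomes priority when not everything can be measured.
- **Table 2 and Primary and Secondary Outcomes.** The ACQ is scheduled at baseline, 6 and 12 months, and its score includes FEV1.

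**The concern.** Whether someone may go on with an intervention and whether her outcome is recorded are separate questions. The safety section settles both with one rule. A person who simply stops attending sessions is pursued for her 12-month ACQ. A willing, contactable person who becomes pregnant is not, and one with a new diagnosis is assessed only with permission.

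These events occur after randomization, and two features make the resulting gaps potentially informative:

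- Evidence-based Intervention Goals associates a 7% weight loss with lower risk of diabetes and cardiovascular disease. Diabetes, coronary heart disease and stroke are among the named triggers, so treatment could affect who falls under the rule.
- One approval covers both intervention and assessment. A physician ruling on the intervention would presumably know the arm. This is an inference, since the blinding section does not address that role.

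At stake is an intention-to-treat estimate with some 12-month values missing by design, possibly unequally between arms.

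**Working it through.** **1. The plan's own figure.** Inputs from Sample Size: N = 324, loss of at most 20%, 259 evaluable, d = 0.4, two-sided 5%, 90% power. Allocation is 1:1.

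- Evaluable: 324 × 0.80 = 259.2, or about 129.5 per arm.
- Power of a two-sample t-test (noncentral t) at 129.5 per arm and d = 0.4: 0.894.
- In the other direction, 90% power needs 133 per arm, 266 in total; 266 / 0.80 = 332.5.

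The stated 324 and 90% reproduce to within rounding.

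**2. Loss of precision.** The document gives no rate of pregnancy or new exclusionary diagnosis, so the extra loss *e* is an assumption. Evaluable N = 324 × (0.80 − *e*):

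| *e* beyond the 20% | Evaluable N | Power at d = 0.4 |
|---|---|---|
| 0 | 259.2 | 0.894 |
| 1% | 256.0 | 0.890 |
| 2% | 252.7 | 0.886 |
| 3% | 249.5 | 0.882 |
| 5% | 243.0 | 0.874 |

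If these losses fall inside the 20%, the first row applies and power is unchanged.

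**3. Possible bias.** Suppose a fraction *f* of one arm is unobserved at 12 months and its mean ACQ differs by *δ* SD from that of the rest of the arm. The full-arm mean equals the observed mean plus *f* × *δ*, so the arm contrast shifts by *f* × *δ*. Again these are assumed values:

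- *f* = 2%, *δ* = 0.25: 0.02 × 0.25 = 0.005 SD
- *f* = 5%, *δ* = 0.5: 0.05 × 0.5 = 0.025 SD
- *f* = 10%, *δ* = 1.0: 0.10 × 1.0 = 0.10 SD

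The design effect is 0.4 SD. The last case requires a tenth of one arm, and nobody in the other, to be removed. Similar losses in both arms would largely cancel.

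**4. Side by side.** Retention seeks outcomes irrespective of adherence. Statistical analysis compares arms as randomized at 12 months. Participant Safety withholds the assessment that supplies the value. Nothing elsewhere says that a pregnant participant, or one refused approval, is still asked for the ACQ.

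**The case against.** Several points on the other side stand.

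- **Nothing is discarded.** A reader might infer that outcome data are deleted or that these participants leave the analysis set. The text limits further participation only. Baseline and any 6-month values can still enter the mixed model, and Table 2 plans record extraction for 12 months after randomization.
- **The diagnosis rule is conditional.** A reader might count every new diagnosis as a lost outcome. The text does not support that; only refused approvals lose data. Pregnancy is the one outright stop.
- **Rates cannot be borrowed freely.** Women planning pregnancy and people with existing diabetes, heart disease, stroke or recently active or treated cancer are excluded at entry. The 20% allowance is not restricted by cause, so it may already absorb these losses. The plan also argues that its t-test calculation is conservative.
- **Detection is not clearly one-sided.** It is tempting to say that sessions expose diagnoses only in the weight-loss arm. Records of all participants are queried every three months and both arms complete scheduled questionnaires, so intervention encounters add some asymmetry but a limited one.
- **The sections can formally coexist.** The retention sentence concerns non-adherence, and intention-to-treat governs how people are analyzed. The plan also names sensitivity analyses for missing values.

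What does not stand is that these provisions settle the matter. Imputation and pattern-mixture models describe missing outcomes under assumptions. They do not recover values that willing participants could have given, and an attrition allowance protects power, not comparability.

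**Conclusion.** The point holds in a limited form. Followed as written, the protocol forgoes the 12-month ACQ after pregnancy and may forgo it after a new exclusionary diagnosis, in both arms. This missingness is avoidable and possibly related to treatment.

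Its size is probably small. Power falls by 0.4 to 2.0 percentage points (0.894 to 0.890-0.874) if an assumed 1-5% is lost beyond the allowance, and not at all otherwise. The illustrative bias is 0.005-0.10 SD, with the top of that range needing an extreme one-sided loss. Both ranges rest on assumed rates and differences, because the document supplies none. A reader might conclude that the trial is materially underpowered or that its intention-to-treat analysis is void; neither follows. The case for acting is that the gap is created by the protocol's own wording and is cheap to close.

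**What to change.** Reconcile Participant Safety, Retention and Statistical analysis by separating two decisions.

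- Leave decisions on the intervention and on physical tests with the study physician; no view is taken here on those clinical rules.
- State that randomized participants who have not withdrawn consent are still asked for the ACQ and the other questionnaires at 6 and 12 months, by phone or online if needed.
- Where spirometry is not done, treat the FEV1 item as missing under the planned missing-data methods, and add a sensitivity analysis for those participants.

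Record extraction and analysis as randomized are already planned and need no new text.

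The cost is about two sentences, possibly an ethics amendment, and a few extra questionnaires. Phone or online completion is already used at screening, and survey software is in place under Data Management. There are two downsides. A few ACQ values will reflect pregnancy or new illness. Those without FEV1 will not be directly comparable with full scores, which matters because the ACQ was chosen partly for including lung function.

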**Recruitment and intervention process measures (monitored continuously)**			
**Safety of participants in the intervention arm (monitored continuously)**			

^1^Pre- and post-bronchodilator spirometry will be obtained at baseline visit 1 to determine reversibility of airway obstruction, which is an eligibility criterion. Only pre-bronchodilator spirometry will be performed at baseline visit 2 and at 6- and 12-month assessments and the measurements obtained will be used for analysis.

^2^Data will be extracted for a period of 12 months before and after randomization.

Abbreviations: ERV, expiratory reserve volume; FEV1, forced expiratory volume in one second; FEV6, forced expiratory volume in six seconds; FVC, forced vital capacity; IC, inspiratory capacity; KPNC, Kaiser Permanente in Northern California; VCin and VCex, inspiratory and expiratory vital capacity; VT, tidal volume.

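### Adverse event ascertainment is unequal by design: reports from WL-only encounters could inflate WL counts of mild events in any by-arm comparison

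*Protocol article*

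**What the plan says.** The Participant Safety section describes two sources that apply to both arms. Surveillance is "by questionnaire at regularly scheduled assessment points and by systematic query of all participants' electronic health records at three month intervals throughout the follow-up". Table 2 agrees: adverse events are listed at baseline, 6 and 12 months with no restriction by arm.

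The same section then adds a further route: "Similar information reported by participants at other times (e.g., during intervention encounters) will be duly noted and followed up to assure participant safety". Intervention encounters are given as an example of those other times. A study physician reviews all adverse event reports, and events go to the IRB, the DSMB and the sponsor.

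Table 2 has a separate row, "Safety of participants in the intervention arm (monitored continuously"), with no matching row for UC.

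The encounters belong to WL: "participants in the WL arm will progress through three successive intervention stages: Intensive, Transitional and Extended stages". Table 3 gives the contacts by stage: "Weekly (13 contacts"), "Monthly (2 contacts") and "Bi-monthly/monthly (typically 3-6 contacts"). Under Extended Stage, participants who regain 3 to 5 lbs "will be telephoned on a biweekly basis until they return to a stable, lower weight", and participants may also contact the interventionists themselves, so the number can be higher.

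**The concern.** After randomization, UC participants have two scheduled occasions on which study staff ask about events, months 6 and 12, plus the record query. WL participants have the same, and also see or speak to study staff about 20 more times. An event mentioned at a session is noted; the same event in a UC participant has to be remembered at the next visit or reach the health record.

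The events most exposed are mild and self-managed. The Intensive Stage sessions include supervised exercise and teach participants to recognize exercise-induced bronchospasm. A strain or a brief episode of bronchospasm may be mentioned that week, yet never lead to a medical contact and be forgotten by month 6. Whether the exercise component is safe in asthma is a question readers will ask of this trial. A by-arm table that mixes the sources could not separate harm from better detection.

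**Working it through.** **1. WL-only contacts.** From Table 3: 13 + 2 + 3 = 18 at the lower end and 13 + 2 + 6 = 21 at the upper end. The text supports the parts: 12 sessions of the parent program plus one added session make 13; one visit in each of months 5 and 6 makes 2; bi-monthly to monthly contact over months 7-12 makes 3 to 6. Calls or visits after weight gain come on top.

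**2. Arm size.** 324 randomized 1:1 gives 324 / 2 = 162 per arm.

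**3. Model.** Let the true risk of a mild event be *p* in both arms. The shared sources capture a fraction *s*. The WL-only route captures a fraction *q* of what they miss. Then

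- observed UC risk = *p s*
- observed WL risk = *p* [*s* + *q*(1 - *s*)]
- apparent risk ratio = 1 + *q*(1 - *s*)/*s*

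The ratio is 1 when *q* = 0, that is, when only the shared sources count. Example: *s* = 0.50 and *q* = 0.50 give WL capture 0.50 + 0.50 × 0.50 = 0.75 and a ratio of 0.75 / 0.50 = 1.50.

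**4. Chance of a nominally significant WL excess.** Two-proportion z-test at 5% two-sided, so 2.5% in the WL direction if capture were equal:

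Φ{(*d* - 1.96 SE0) / SE1}, with *d* the difference in observed risks, SE0 the pooled and SE1 the unpooled standard error.

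For *p* = 0.40, *s* = 0.50 and WL capture 0.75, the observed risks are 0.20 and 0.30. SE0 = √(0.25 × 0.75 × 2/162) = 0.0481. SE1 = √(0.30 × 0.70/162 + 0.20 × 0.80/162) = 0.0478. (0.10 - 1.96 × 0.0481)/0.0478 = 0.119, and Φ(0.119) = 0.547.

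**5. Range.** The values of *p* and both capture fractions are assumptions; none is in the documents.

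| Capture by shared sources (UC) | Capture in WL | Apparent risk ratio | *p* = 20% | *p* = 30% | *p* = 40% |
|---|---|---|---|---|---|
| 95% | 97% | 1.02 | 3.1% | 3.3% | 3.5% |
| 80% | 90% | 1.13 | 6.9% | 9.0% | 11.5% |
| 60% | 75% | 1.25 | 12.1% | 17.0% | 22.8% |
| 50% | 65% | 1.30 | 13.2% | 18.7% | 24.9% |
| 50% | 75% | 1.50 | 27.4% | 40.8% | 54.7% |

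The first row is the plausible region for serious or medically attended events, which the record query should find in both arms. The lower rows could apply only to mild events that leave no record.

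**The case against.** The strongest reply is that the harmed analysis is not in the document. Adverse events are not among the primary or secondary outcomes, the Statistical analysis section does not mention them, and Participant Safety describes case-by-case review and reporting, not arm-level counts. Table 2 even keeps the scheduled adverse event row apart from the intervention-arm monitoring row. A source field and tabulation rules could sit in the full protocol, the forms or the SAP, which are not shown. This stands against any claim that the plan pools the sources. It does not remove the asymmetry, which the article states as a design feature.

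Two stronger readings are tempting. A reader might infer that adverse events are collected at each of the 18-21 contacts. The text supports only that volunteered reports are noted; no questioning at sessions is described, and because encounters are only an example, the route is not formally closed to UC. A reader might also infer that the safety comparison will show a false excess in WL. No such comparison is planned in the article, and with high shared capture the distortion is negligible.

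Further, unequal contact is inherent in an unblinded behavioral trial against usual care, noting volunteered events is a safety duty, and the bias overstates harm in WL and does not hide it. All of this is fair, and is why the remedy concerns tabulation only.

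Lastly, restricting by source does not equalise ascertainment fully: a WL participant referred for evaluation after an encounter can enter the health record and so the shared stream. That is correct, and the fix allows for it.

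**Conclusion.** The concern holds in conditional form. The article itself sets up unequal ascertainment, through reports noted at WL-only encounters and continuous safety monitoring named for one arm. If those reports are counted in a by-arm comparison, a spurious WL excess is possible, mainly for mild events without medical contact. Serious and medically attended events should be little affected, because the questionnaires and the record query cover both arms.

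The size is not known. Under equal true risk of 20-40% and 162 per arm, the chance of a false signal runs from about 3%, hardly above the nominal 2.5%, to about 55% in the least favorable case shown. The upper figures depend wholly on assumed low capture by the shared sources. The primary ACQ result is not touched.

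**What to change.** Add a source field to the adverse event form (scheduled questionnaire, record query, intervention encounter, other). State in the plan that any between-arm comparison, in DSMB tables or the trial report, rests on the questionnaire and the record query used in both arms, and that events first reported at intervention encounters are listed separately for WL. Flag record-query events that followed a referral from an encounter, and state that some residual asymmetry remains. Reporting and follow-up of individual events do not change.

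The cost is one form field, one flag and a short statement. The downside is that the comparative table omits some true WL events; they stay visible in the separate listing. The field should be in place from the start of data collection, since the source is hard to reconstruct later.
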